### Design

This is an open-label, multicenter, randomized, controlled, parallel group, intent-to-treat, superiority clinical trial. Figure 1 illustrates the trial design, and Table 1 summarizes the timing of the trial. All participants receive the intervention in a single oral intake on the day of inclusion. Treatment allocation is carried out according to a 1:1 ratio by means of dynamic randomization (randomization by minimization) taking into account 6 criteria: worsening risk factor (age ≥ 75 years, or oxygen dependence characterized by a peripheral capillary oxygen saturation [SpO2] ≤ 94% in room air, or ratio of partial oxygen pressure [PaO2] to oxygen fraction in the inspired air [FiO2] ≤ 300 mmHg), criterion used for COVID-19 diagnosis (RT-PCR or chest CT scan), hospitalization (yes/no), concomitant use of anti-infective drugs such as hydroxychloroquine or azithromycin among others, concomitant use of corticosteroids, and recruiting center. This dynamic randomization is established by the Department of Biostatistics and Methodology of the University Hospital of Angers, France. Randomization is performed using a web-based system (Ennov Clinical®).

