### Planned eligibility criteria

#### Inclusion criteria

People are eligible to participate if they are 65 years and over, if they have a SARS-CoV-2 infection diagnosed within the preceding 3 days by RT-PCR and/or chest CT scan, and if they have at least one worsening risk factor (age ≥ 75 years, or SpO2 ≤ 94% in room air, or PaO2/FiO2 ≤ 300 mmHg). Participants must be covered by or having the rights to medical care insurance. Participants must also have given and signed an informed consent form to participate in the trial (or informed consent form obtained from the trusted person, or emergency inclusion procedure in the context of lockdown, as appropriate).

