#### Analyses

The effect of high-dose vitamin D supplementation compared to standard-dose vitamin D supplementation will be determined using evaluation criteria, which are the mortality rates and the changes in OSCI score within 14 and 28 days of inclusion, using respectively the chi-square test or exact Fischer test, and independent samples *t* test or Mann-Whitney *U* test, as appropriate. An interim analysis of 100 participants is planned. It will focus on the primary outcome measure (i.e., all-cause mortality within 14 days of inclusion) with a *P* value of 0.001 used as the significance threshold for stopping the study. The final analysis of the primary outcome measure will use the *P* value of 0.0498 as the significance threshold (Peto-Haybittle method).

The proportions of participants with at least one serious adverse event within 28 days of inclusion will be compared using the chi-square test (or exact Fisher test if necessary). Survival curves will be plotted from baseline to day 28 using the Kaplan-Meier method, and a Cox proportional hazards model will be used to compare clinical outcomes between groups. The log-linearity assumptions will be checked for each quantitative variable introduced in the Cox models, and proportional hazards assumption will be checked for each variable to confirm adequacy for the Cox models.

Any exploratory analyses here will use multivariate logistic and proportional hazards regression. In addition, the stratification criterion for randomization will be also taken into account in the multivariate models. Excessive subgroup analyses can give rise to misleading results, and therefore, all subgroup investigations will be interpreted cautiously. In particular, subgroup analysis will be conducted depending on the severity of hypovitaminosis D at baseline and at day 7.

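### The primary mortality test is unadjusted although allocation is minimised on six criteria: valid, but conservative, and it forgoes a small gain in power that costs almost nothing

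*Protocol article*

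**What the plan says.** **Allocation (Design).** "Treatment allocation is carried out according to a 1:1 ratio by means of dynamic randomization (randomization by minimization) taking into account 6 criteria". The six are the worsening risk factor, the diagnostic criterion, hospitalisation, anti-infective use, "concomitant use of corticosteroids, and recruiting center".

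**Prognosis (Inclusion criteria).** Every participant must have "at least one worsening risk factor (age ≥ 75 years, or SpO2 ≤ 94% in room air, or PaO2/FiO2 ≤ 300 mmHg"). The protocol therefore treats these characteristics as predictors of a worse course, but it gives no strength of association.

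**Primary analysis (Analyses).** Mortality and ordinal-scale changes are compared "using respectively the chi-square test or exact Fischer test, and independent samples" *t* test or Mann-Whitney test. The final threshold for the primary outcome is 0.0498, after an interim analysis of 100 participants at 0.001.

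**Adjustment (Analyses).** A later paragraph opens with "Any exploratory analyses here will use multivariate logistic and proportional hazards regression" and then says that "the stratification criterion for randomization will be also taken into account in the multivariate models".

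**Sizing (Sample size calculation).** Two crude proportions: 20% against a 12-point lower rate, two-sided 5%, 80% power, 125 per group, 260 in total after 5% loss.

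**The concern.** Minimisation forces the arms to be alike on the chosen factors. Where those factors predict death, the difference in death rates varies less from trial to trial than it would under simple randomisation. The chi-square variance does not know this. It is too large for the design, and the test rejects too rarely under the null.

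An analysis that includes the minimisation factors recovers that precision. The protocol does not leave the matter open: it names a crude test for the primary comparison and places adjustment in a paragraph on exploratory work. At stake is efficiency. The trial has little slack in its sample size, and its Ethical considerations section concedes that it may be underpowered for effects smaller than 12 points.

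**Working it through.** **1. Reproduce the plan's own figure.** Inputs: 20% v 8%, two-sided 0.05, power 80%, so (1.960 + 0.842)² = 7.849.
- Arcsine formula: 7.849 / [2 × (0.4636 − 0.2868)²] = 125.4, i.e. 126 per group.
- Unpooled normal formula: 7.849 × (0.16 + 0.0736) / 0.12² = 127.3, i.e. 128 per group.
- Power at 125 per group, pooled formula: SE under the null = √(2 × 0.14 × 0.86 / 125) = 0.0439; SE under the alternative = √(0.2336 / 125) = 0.0432; Φ[(0.12 − 1.960 × 0.0439) / 0.0432] = 78.4%.

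The stated 125 is reproduced closely enough, and it belongs to a crude comparison.

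**2. Analytic approximation.** Let R² be the share of outcome variance explained by the balanced factors (an assumption; the protocol gives none), and suppose balance is complete. The true SE is then √(1 − R²) times the crude one. With z = 1.962 for 0.0498:
- true size of the crude test = 2Φ(−1.962 / √(1 − R²));
- crude power = Φ[(0.12 − 1.962 × 0.0439) / (0.0432 × √(1 − R²))];
- adjusted power: the same, with 0.0439 also multiplied by √(1 − R²).

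| Assumed R² | Size, crude | Power, crude | Power, adjusted |
|---|---|---|---|
| 0 | 4.98% | 78.4% | 78.4% |
| 2% | 4.75% | 78.6% | 79.2% |
| 8% | 4.08% | 79.3% | 81.7% |
| 16% | 3.23% | 80.4% | 85.0% |

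**3. Simulation.** Assumptions: 250 evaluable patients, minimisation with a biased coin of 0.8, 10 centres, threshold 0.0498, 24,000 trials per scenario. Factor prevalences and strengths are also assumed. The adjusted analysis is a standardised risk difference using the five non-centre factors.

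| Factors | Size, crude | Size, adjusted | Power, crude | Power, adjusted |
|---|---|---|---|---|
| Not prognostic | 4.9% | 5.2% | 79.6% | 80.2% |
| Weak (AUC about 0.61, R² about 2%) | 4.7% | 5.2% | 79.4% | 80.4% |
| Moderate (AUC about 0.70, R² 7–9%) | 4.0% | 5.1% | 80.0% | 82.5% |
| Strong (AUC about 0.78, R² 15–17%) | 3.5% | 5.2% | 80.9% | 85.4% |

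The Monte Carlo standard error is about √(0.0498 × 0.9502 / 24,000) = 0.14 points for size and √(0.8 × 0.2 / 24,000) = 0.26 points for power. The pattern agrees with step 2.

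**4. What the model can carry.** Expected deaths at the final analysis: 125 × 0.20 + 125 × 0.08 = 25 + 10 = 35. At the interim with 50 per arm: 10 + 4 = 14. In the same simulations, a logistic test of the treatment term ran at a size of 5.3% to 5.6%, and at about 6% with ten centres as fixed terms. The standardised risk difference, with centre left out, stayed at 5.1% to 5.2%.

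**The case against.** The strongest reply is that nothing is broken. A chi-square after minimisation keeps type I error at or below nominal, sizing and analysis both use crude proportions, and adjusted models are already planned as support. With few deaths, a simple primary test is defensible. All of this stands, and it makes the point one of efficiency and not of validity.

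Three further objections also stand in part. First, the size of the gain rests on assumed prognostic strengths. Second, at the low end some of it is not efficiency: with non-prognostic factors, power still moves from 79.6% to 80.2% because the adjusted test runs slightly above the threshold. Third, a logistic model is a poor replacement at about 35 deaths, and no adjusted model suits an interim with about 14. The fix below is shaped by these limits.

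A reader might infer that the plan loses power it was counting on. It does not: crude power is 78.4% by the pooled formula and about 80% in simulation, which is what was planned.

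A reader might also infer that the worsening risk factor carries no information as a minimisation criterion, because every participant has one. The documents do not support that. The Design section lists the components beside the criterion, those components vary between patients, and nothing says it was coded as a single yes/no item.

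What the reply does not answer is why factors that the trial already collects and balances on should be kept out of the primary comparison. An analysis plan that made an adjusted test primary would depart from the protocol's stated choice, so this is not a detail merely deferred.

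**Conclusion.** The point holds as a modest inefficiency. The primary test is valid and meets the planned power. Under weak to strong prognostic factors it is conservative, with true type I error of about 3.5% to 4.7% against 4.98%, and it gives up about 1 to 4.5 points of power that minimisation makes available. If the factors do not predict death, the gain is about nil.

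The direction is secure wherever the factors are prognostic, and the protocol treats at least one of them as such. The magnitude depends on assumed prognostic strength, factor prevalence and the biased-coin probability, none of which the protocol states.

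**What to change.** Amend the Analyses section before unblinded comparative data are seen:

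- **Final primary analysis:** a covariate-adjusted risk difference for 14-day mortality with its confidence interval, obtained by standardisation (g-computation), tested at 0.0498.
- **Covariates:** diagnostic criterion, hospitalisation, anti-infective use, corticosteroid use, and the worsening risk factor entered as its components (age 75 years or over; oxygen criterion). List them by name, since the present wording refers to one stratification criterion where the Design section has six.
- **Centre:** a random effect or pooled categories, not ten or more fixed terms.
- **Fallback:** a named penalised model in case of non-convergence or separation.
- **Sensitivity analysis:** the chi-square test as now written.
- **Interim at 100 participants:** keep the crude or exact test at 0.001.
- **Cox model:** adjust for the same covariates.

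The cost is wording only, because the factors have to be known at allocation. The downside is that about 35 deaths limit the model, so the type I error of the adjusted test may be very slightly above nominal (5.1% to 5.2% in simulation).

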### Statistics

#### Sample size calculation

The trial aims to recruit 260 patients divided into 2 groups of 130 patients. Based on previous literature, the expected death rate in the standard-dose vitamin D group is estimated at 20% in this population with worsening risk factors [35]. A total of 125 participants per group should be involved to demonstrate, under a bilateral hypothesis, a between-group absolute difference in all-cause mortality risk of 12% with an alpha risk of 5% and a power of 80%. Such target is consistent with one previous study in an intensive care unit reporting a 17% mortality rate reduction in patients who received high-dose vitamin D compared to a placebo [27]. Taking into account the loss to follow-up (estimated at 5%), it is necessary to include a total of 260 subjects (130 per group).

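### The final threshold of 0.0498 fits an interim look at about half the information; for the planned look at 100 of 260 participants the matching value is 0.0496

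*Protocol article*

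**What the plan says.** The Sample size calculation section works "under a bilateral hypothesis" and "with an alpha risk of 5% and a power of 80" per cent. On size it says "The trial aims to recruit 260 patients divided into 2 groups of 130 patients", built up from 125 per group with a 5% allowance for loss to follow-up.

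The Analyses section says "An interim analysis of 100 participants is planned". That look concerns 14-day all-cause mortality, with P = 0.001 as the threshold for stopping. For the final analysis of the same outcome it fixes a P "value of 0.0498 as the significance threshold (Peto-Haybittle method").

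The section therefore gives both the timing of the look and the final threshold. No other part of the article places the look at half the patients or gives another basis for 0.0498.

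**The concern.** A final threshold a little below 0.05, given to four decimals, is a correction for the error already spent at the interim look. That correction depends on timing. The earlier the look, the weaker the correlation between the interim and final statistics, the more the interim rejections add to the final ones, and the lower the final threshold must be. A value that suits a half-way look is slightly too generous for a look at 100 of 260.

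At stake is whether the confirmatory threshold for the primary outcome follows from the design that it is stated for. The practical stake is small, and the size is worked out below.

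**Working it through.** **Inputs, all from the Statistics section**

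- Overall two-sided error: 0.05 (Sample size calculation).
- Interim threshold a1 = 0.001, taken as two-sided; final threshold a2 = 0.0498 (Analyses).
- Interim at 100 participants (Analyses).
- Final number: 260 planned; 250 before the allowance for loss; 260 × 0.95 = 247 after 5% loss.

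**Information fraction.** t = 100/260 = 0.385, 100/250 = 0.400 or 100/247 = 0.405.

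**Method.** Under the null, the interim and final statistics Z1 and Z2 are bivariate standard normal with correlation √t. With c1 = z(1 − 0.001/2) = 3.2905 and c2 = z(1 − a2/2),

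overall error = 1 − P(|Z1| < c1 and |Z2| < c2).

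This is evaluated by numerical integration and solved for the a2 that gives 0.05.

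**Reproducing the plan's figure.** At t = 0.50 the solution is a2 = 0.04978, which rounds to 0.0498. The solution rounds to 0.0498 only for t between about 0.48 and 0.56, which is about 125 to 147 of 260 participants.

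**At the stated timing**

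| Look | t | Final threshold for 5% | Overall error with 0.0498 |
|---|---|---|---|
| 100 of 260 | 0.385 | 0.04962 | 0.05018 |
| 100 of 250 | 0.400 | 0.04964 | 0.05016 |
| 100 of 247 | 0.405 | 0.04965 | 0.05015 |
| half-way | 0.500 | 0.04978 | 0.05002 |

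The third threshold is 0.049647 before rounding, so all three denominators give 0.0496 to four decimals.

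**Other routes to 0.0498.** A Bonferroni split gives 0.05 − 0.001 = 0.049. The simple Haybittle-Peto convention leaves the final test at 0.05, with overall error 0.0504 at t = 0.385. Neither gives 0.0498.

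**Does the excess survive in the planned test?** The chi-square and Fisher tests on death counts are discrete. Exact enumeration of the uncorrected chi-square test, with 50 then 130 per arm and thresholds 0.001 then 0.0498, gives overall error 0.0498 at a null death rate of 8%, 0.0489 at 14% and 0.0501 at 20%. Replacing 0.0498 by 0.0496 leaves each value unchanged. The reason is that with 130 in each arm no chi-square table, with or without continuity correction, has P between 0.0496 and 0.0498. A search of Fisher's test up to 59 deaths per arm found none either.

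Other arm sizes do have such tables. Examples for the uncorrected chi-square test are 22 against 35 deaths with 124 per arm (P = 0.04975), and 39 against 54 with 125 per arm (P = 0.04967).

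**Cost in power.** For 20% against 8% with 130 per group, an unpooled normal calculation for the final test gives 80.76% at 0.0498 and 80.72% at 0.0496, a loss of about 0.05 percentage points.

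**The case against.** The strongest reply is that nothing practical turns on this. The nominal excess is 0.0002. In the exact enumeration the error falls on both sides of 5%, and with 130 per arm the two thresholds reject the same chi-square tables. A Haybittle-Peto rule is meant to leave the final level almost untouched, and the plan's 0.0498 is already stricter than the plain 0.05. All of this stands, and it limits the point to a minor correction.

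A reader might infer that the trial's overall type I error really exceeds 5%. The document does not support that. The 5.02% is a large-sample value, and for the discrete tests that the plan names the actual error can lie just below or just above 5%, depending on the death rate.

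A second reply is that the true information fraction will be known only at the interim, and that such detail belongs in an analysis plan or monitoring charter. This is fair as far as recomputation goes. It does not remove the mismatch, because the article itself fixes both the look at 100 and the value 0.0498, and each denominator that the article supports leads to 0.0496.

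A reader might also want a confidence level matched to the threshold. The Analyses section states none, so there is nothing there to correct.

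**Conclusion.** The point holds as a minor arithmetic correction. The stated final threshold does not follow from the stated interim timing: 0.0498 belongs to a look at about half the information, and 0.0496 belongs to a look at 100 of 250 to 260 participants. The nominal overall error is 5.02% instead of 5%, an excess smaller than the discreteness of the test. A decision would differ only if the final P value fell between 0.0496 and 0.0498, which equal arms of 130 do not allow with the chi-square test and some other arm sizes do.

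This rests on three assumptions: one interim look, a two-sided 0.001 at that look, and information proportional to the number of participants. It does not show that the trial fails to control its error in any way that matters.

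**What to change.** In the Analyses section, replace 0.0498 by 0.0496 for an interim at 100 of 260 participants. Alternatively, state that the final threshold will be recomputed from the actual information fraction at the interim so that the overall two-sided error is 5%. Either is a change of one number or one sentence, with no change to the sample size and a power loss of about 0.05 percentage points.

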## Methods

### Objectives

The primary objective is to compare the effect of a single oral high dose of cholecalciferol versus a single oral standard dose of cholecalciferol on 14-day all-cause mortality rate in older adults infected with SARS-CoV-2 at higher risk of worsening.

The secondary objectives of the study are as follows:
To compare the effect of high-dose versus standard-dose cholecalciferol on 28-day all-cause mortality rateTo compare the effect of high-dose versus standard-dose cholecalciferol on the clinical course of the disease (i.e., change of World Health Organization’s [WHO] Ordinal Scale for Clinical Improvement [OSCI] scale for COVID-19) within 14 and 28 days of inclusion [29]To compare the safety of high-dose versus standard-dose cholecalciferolTo compare the effect of high-dose versus standard-dose cholecalciferol on all-cause mortality rate and OSCI scale changes within 14 and 28 days of inclusion in the subgroup with vitamin D deficiency at baseline (i.e., serum 25(OH)D < 25 nmol/L)To determine the impact of serum 25(OH)D concentration at day 7 (i.e., serum 25(OH)D concentration < 75 nmol/L versus ≥ 75 nmol/L) on mortality rate and OSCI scale changes within 14 and 28 days of inclusionTo determine, in the subgroup with vitamin D deficiency at baseline (i.e., serum 25(OH)D < 25 nmol/L), the impact of the serum 25(OH)D concentration reached at day 7 (i.e., serum 25(OH)D concentration < 75 nmol/L versus ≥ 75 nmol/L) on mortality rate and OSCI scale changes within 14 and 28 days of inclusionTo model survival and clinical course (OSCI scale changes) within 14 and 28 days of inclusion according to the change of serum 25(OH)D concentration between day 0 and day 7To compare the mortality rates observed within 14 days of inclusion in each arm of the study with the mortality rates reported in the French hospital geriatric units receiving COVID-19 patients

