#### “Intervention” group

All participants receive the high-dose cholecalciferol (vitamin D_3_) supplement in a single oral intake on the day of inclusion (Mylan; 75008 Paris, France). Cholecalciferol is packaged in a drinking vial of 2 mL containing 200,000 IU. Thus, participants in the Intervention group take two vials at once, to reach the studied total dose of 400,000 IU. Vitamin D is ideally taken during food intakes because vitamin D is lipophilic and therefore better absorbed with fat. Such high dose is expected to quickly raise the serum 25(OH)D concentration above 75 nmol/L [30], which is not expected with lower doses [23]. This is all the more important in that, based on the knowledge of vitamin D non-skeletal effects, it appears that raising serum 25(OH)D concentrations above 75 nmol/L is necessary to obtain antiviral effect [4]. Finally, it has to be quoted that the chosen dose of 400,000 IU does not reach the dose of 500,000 IU that has been previously associated with side effects [31]. In addition, participants in the Intervention group will not take other vitamin D supplements for 45 days and will therefore receive the equivalent of a daily dose of 8900 IU/day over the period, less than the toxic dose of 10,000 IU/day [28].

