#### Blood sample collection procedures

All participants are tested for 25(OH)D concentration at baseline and day 7 (± 1 day). Blood tests are done by a clinical research nurse. Serum 25(OH)D concentration is measured with radioimmunoassay (RIA) kits in each recruiting center. RIA kits recognize both vitamins D_2_ and D_3_. With this method, there is no interference of lipids, which is often observed in other non-chromatographic assays of 25(OH)D. The intra- and interassay precisions are respectively 5.2% and 11.3% (range in normal adults aged 20–60 years, 75–310 nmol/L). Creatinine, calcium, and albumin (to estimate corrected calcemia) are also measured at baseline and day 7 (± 1 day) with standard laboratory methods.

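### The day-7 25(OH)D analyses use a post-randomisation value that only day-7 survivors can have, so they give non-randomised associations from about day 7, not an impact on outcomes from inclusion

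*Protocol article*

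**What the plan says.** In the protocol article, Methods, Objectives, one secondary objective is "To determine the impact of serum 25(OH)D concentration at day 7", split at 75 nmol/L, on mortality and OSCI change within 14 and 28 days of inclusion. A second repeats this in participants deficient at baseline (below 25 nmol/L). A third models survival and clinical course over the same windows by the change in 25(OH)D from day 0 to day 7.

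Under Statistics, Analyses, the plan adds that "subgroup analysis will be conducted depending on the severity of hypovitaminosis D at baseline and at day 7". The same section says "Survival curves will be plotted from baseline to day 28 using the Kaplan-Meier method" and that "all subgroup investigations will be interpreted cautiously". It also says that exploratory analyses will use multivariate regression taking the randomisation criterion into account.

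The blood sample section puts the second sample at day 7, give or take one day. Dosing is on the day of inclusion. The section on the Intervention group says of the 400,000 IU dose: "Such high dose is expected to quickly raise the serum 25(OH)D concentration above 75 nmol/L [30], which is not expected with lower doses".

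**The concern.** A participant who dies before the day-7 sample has no day-7 value. The classification is therefore available only to people who have already survived about half of the 14-day window, yet the outcome clock starts at inclusion.

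The value is also a consequence of treatment. If the high dose is expected to pass 75 nmol/L and lower doses are not, a high-dose participant below the cut-off and a standard-dose participant above it are both atypical of their arms. Comparing arms within a day-7 stratum compares groups that randomisation did not make alike. Comparing <75 with ≥75 mixes arm, baseline level and whatever aspects of illness affect 25(OH)D.

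At stake is interpretation. The protocol argues that a level above 75 nmol/L is needed for an antiviral effect and concedes that the trial may be underpowered for smaller mortality effects. If the primary result were null, a finding that those who reached 75 nmol/L survived more often could be read as evidence of mechanism. The word *impact* invites that reading.

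**Working it through.** **Figures in the plan.** None is given for the day-7 analyses. The nearest is 125 per group for 20% versus 8% mortality (two-sided 5%, power 80%). By the arcsine formula, n = 2(1.960 + 0.842)² / h² with h = 2·asin√0.20 − 2·asin√0.08 = 0.354, so n = 125.4. This confirms the 8% implied for the high-dose arm. Expected 14-day deaths are 130 × 0.20 + 130 × 0.08 = 36.4.

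**Step 1: what is estimated among those sampled.** Let m be 14-day mortality and e the share of those deaths that precede the sample (e is not in the document). The fraction with no value is m·e. Mortality among the rest is m(1 − e)/(1 − m·e). With m = 20%:

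| e | No day-7 value | 14-day mortality among those sampled |
|---|---|---|
| 30% | 6% | 0.14/0.94 = 14.9% |
| 50% | 10% | 0.10/0.90 = 11.1% |
| 60% | 12% | 0.08/0.88 = 9.1% |

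This is mortality from about day 7 to day 14, not mortality over 14 days from inclusion. On the planning rates with e = 40%, 36.4 × 0.40 = 14.6 deaths drop out and about 22 remain.

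**Step 2: bias with early deaths excluded.** Simulated null: 130 per arm, 20% mortality in both, no effect of arm or 25(OH)D on death. Assumptions: e = 50%; day-7 25(OH)D mean 100 (high dose) and 55 (standard) nmol/L, SD 25. An unmeasured severity score raises the log-odds of death by 1 or 1.5 per SD and lowers 25(OH)D by 0 to 12.5 nmol/L per SD.

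| Log-odds of death per SD | Fall in 25(OH)D per SD | OR, ≥75 v <75 | False-positive rate | OR, high v standard, within <75 | within ≥75 |
|---|---|---|---|---|---|
| 1 | 0 | 1.00 | 5% | 1.00 | 0.99 |
| 1 | 8 | 0.74 | 11% | 1.39 | 1.34 |
| 1 | 12.5 | 0.62 | 20% | 1.65 | 1.64 |
| 1.5 | 12.5 | 0.55 | 32% | 1.85 | 2.10 |

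Mortality by randomised arm stayed at 20% versus 20% throughout.

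**Step 3: milder confounding.** Assumptions: mortality 14% to 16%; e = 40%; baseline mean 45, SD 20 nmol/L; mean rise 50 versus 8 (SD 20 and 8); odds ratio 2 for death per SD of severity; severity correlated −0.2 with baseline level and −0.3 with rise. The risk ratio for ≥75 versus <75 is 0.81. Between arms, mortality is 12.7% v 10.4% below 75 (12.7/10.4 = 1.22) and 9.1% v 7.6% above (9.1/7.6 = 1.20). At 260 participants the false-positive rate for ≥75 versus <75 is 7.4% (8% to 9% in a repeat run). For arms within strata it is about 7% (<75) and 3% (≥75).

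**Step 4: early deaths placed in <75.** This needs a rule that the document does not contain. With the Step 2 distributions and no confounding, P(≥75) = ½[Φ(1) + 1 − Φ(0.8)] = 0.527. With e = 50%, mortality above the cut-off is 11.1%. Below it, mortality is (0.10 + 0.90 × 0.473 × 0.111)/(0.10 + 0.90 × 0.473) = 28.0%. The OR is (0.111/0.889)/(0.280/0.720) = 0.32. For e = 30% and 60% it is 0.52 and 0.24. Simulated false-positive rates run from 52% to 99%.

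**The case against.** A reader might infer that the plan builds in strong immortal-time bias, halving apparent mortality above 75 nmol/L or worse. The document does not support that. The groups are defined by a measured concentration, so a participant without a sample belongs to neither. No sentence puts early deaths in the low group, and handling of missing values may sit in a full protocol or analysis plan that is not shown. With early deaths left out and severity unrelated to 25(OH)D, the time origin alone creates no bias (OR 1.00, error about 5%). What remains is then a wrong label. A time-varying exposure is also not ruled out.

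The subgroup sentence is ambiguous as well. In the Objectives, the only comparison of doses in a subgroup is in those deficient at baseline; the day-7 objectives compare concentrations, not arms. The sentence may only summarise both.

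Finally, the exploratory models account for the randomisation criteria, which include age ≥75 and oxygenation. These analyses are secondary, and cautious interpretation is promised.

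Most of this stands and limits the point's size and rank. It does not remove it. Cautious reading does not correct bias. The minimisation factors include neither baseline 25(OH)D nor arm. The window from inclusion and the causal wording are stated in the article itself.

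**Conclusion.** The concern holds as a should-fix matter. As worded, the day-7 analyses classify participants by a consequence of treatment that only day-7 survivors have, while claiming an impact on outcomes from inclusion. Comparing arms within day-7 strata, if that is what is meant, would break randomisation and could show false harm of the high dose when severity also affects 25(OH)D. The <75 versus ≥75 contrast is a confounded association with mortality after about day 7.

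The direction follows from the structure; the size does not. Depending on how strongly severity is tied to 25(OH)D, the null odds ratio for ≥75 versus <75 ran from 1.00 to 0.55 and the false-positive rate from 5% to 32%. The early-death share, the 25(OH)D distributions and the severity links are all assumptions. Large immortal-time bias arises only if early deaths are classed as <75, which the document neither states nor excludes. Nothing here touches the primary intention-to-treat comparison or the baseline-defined subgroup.

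**What to change.** - In Analyses, remove day 7 from the subgroup analysis of the treatment effect and keep the baseline subgroup.
- Recast the day-7 objectives and the day 0 to day 7 change objective as landmark analyses. Include participants alive and sampled at day 7, and count deaths and OSCI change from the sample date to day 14 and day 28.
- State that deaths before the sample are never assigned to <75 nmol/L, and report them by arm.
- Adjust sparingly: arm, baseline 25(OH)D and one baseline severity measure. About 22 deaths may remain, too few for a long covariate list.
- In the baseline-deficient subgroup, describe only. With an assumed baseline mean of 45 and SD of 20, P(<25) = Φ(−1) = 0.159, or about 41 of 260 participants, with 41 × 22/260 = 3 to 4 deaths after the landmark.
- Replace *impact* with *association* and acknowledge residual confounding. A landmark removes the survival-time problem, not the confounding.

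The cost is a change of wording and no new data. The price is fewer events and lower precision in these secondary analyses.
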